### 9.3.7 Phone Visit 4 – Follow-up

Intervention arm:

This visit will be conducted about two weeks after the end of the treatment period for follow-up and safety outcomes (AE/SAE assessment), only for the participant in the intervention arm.

### 9.3.8 Others

Additional visits may be conducted in the event of premature discontinuation of the IMP. The assessments for the premature discontinuation (PD) visit will mirror those of visit 4 (end of intervention) and should be scheduled at the time of IMP discontinuation. A phone follow-up should be conducted two weeks after the PD visit to monitor safety outcomes (AE/SAE assessment). Additionally, at any point in the study, an unscheduled visit may be performed, if needed, at the investigator's discretion (the assessments for this unscheduled visit will be oriented/performed under clinical criteria).

## 10. SAFETY

### 10.1 Drug studies

#### 10.1.1 Definition and Assessment of (Serious) Adverse Events and Other Safety-Related Events

An **Adverse Event (AE)** is any unfavorable medical event in a participant in a clinical investigation who has been administered a pharmaceutical product, and it does not necessarily have a causal relationship with the study procedure. An AE can, therefore, be any unfavorable and unintended sign (including an abnormal laboratory finding), symptom, or disease temporally associated with the use of a medicinal (investigational) product, whether related to the medicinal (investigational) product. [ICH E6 1.2]

A **Serious Adverse Event (SAE)** is classified as any untoward medical occurrence that:

- results in death,
- is life-threatening,
- requires in-patient hospitalization or prolongation of existing hospitalization,
- results in persistent or significant disability/incapacity, or
- is a congenital anomaly/birth defect.

In addition, important medical events that may not be immediately life-threatening or result in death or require hospitalization but may jeopardize the participant or may require intervention to prevent one of the other outcomes listed above should also usually be considered serious. [ICH E2A]

SAEs should be followed until resolution or stabilization. Participants with ongoing SAEs at study termination (including safety visit) will be further followed up until recovery or until stabilization of the disease after termination.

Examples of such events are intensive treatment in an emergency room or at home for allergic bronchospasm, blood dyscrasias, or convulsions that do not result in hospitalization or the development of drug dependency or drug abuse.

#### Adverse Drug Reaction (ADR)

An adverse reaction is an adverse event for which the causal relationship between the study drug and the Adverse Event is suspected.

#### Serious Adverse Reaction (SAR)

An adverse event that fulfills both the criteria for SAE and ADR.

#### Medical event of special interest (MESI)

A MESI is an event that, in evaluating safety, has a special focus. A MESI is an AE (SAE or non-serious AE) that fulfills one or more of the below-defined MESI criteria:

Medication errors concerning trial products:

- Administration of the wrong drug
- Wrong route of administration, such as intramuscular instead of subcutaneous
- Accidental administration of a lower or higher dose than intended; however, the administered dose must deviate from the intended dose to an extent where clinical consequences for the trial participant were likely to happen as judged by the investigator, although not necessarily did happen. Overdose and missed insulin bolus resulting in severe hypoglycemia or hyperglycemia are considered AE or SAE, depending on severity.

#### Unexpected Adverse Drug Reaction

An “unexpected” adverse drug reaction is an adverse reaction, the nature or severity of which is not consistent with the applicable product information [ICH E2A].

#### Suspected Unexpected Serious Adverse Reactions (SUSARs)

The Sponsor/Investigator evaluates any SAE that has been reported regarding seriousness, causality, and expectedness. If the event is related to the study drug and is both serious and unexpected, it is classified as a SUSAR.

#### Assessment of Causality

Both Investigator and Sponsor-investigator will make a causality assessment of the event to the study drug based on the criteria listed in the ICH E2A guidelines:

| Relationship                                                                                | Description                                                                                                                  |
|---------------------------------------------------------------------------------------------|------------------------------------------------------------------------------------------------------------------------------|
| Definitely                                                                                  | Temporal relationship
Improvement after dechallenge*
Recurrence after rechallenging.
(or other proof of drug cause) |
| Probably                                                                                    | Temporal relationship
Improvement after dechallenge
No other cause evident                                             |
| Possibly                                                                                    | Temporal relationship
Other cause possible                                                                                |
| Unlikely                                                                                    | Any assessable reaction that does not fulfill the above conditions                                                           |
| Not related                                                                                 | A causal relationship can be ruled out                                                                                       |
| *Improvement after dechallenge only taken into consideration, if applicable to the reaction |                                                                                                                              |

### Assessment of Severity

The investigator will assess the severity of each AE/SAE reported during the study and assign it to 1 of the following categories:

- Mild: An event that is easily tolerated by the participant, causing minimal discomfort and not interfering with everyday activities.
- Moderate: An event that causes sufficient discomfort and interferes with everyday activities.
- Severe: An event that prevents everyday activities. An AE assessed as severe should not be confused with an SAE. Severe is a category utilized for rating the intensity of an event, and both AEs and SAEs can be assessed as severe (an event is defined as 'serious' when it meets at least 1 of the predefined outcomes as described in the definition of a SAE, NOT when it is rated as severe).

### 10.1.2 Reporting of serious adverse events (SAE) and other Safety-Related events

During the entire duration of the study, all AEs and all serious adverse events SAEs will be collected, fully investigated, and documented in source documents and eCRF. Study duration encompasses when the participant signs the informed consent until the last protocol-specific procedure has been completed, including a safety follow-up period.

#### Reportable AEs for Hypoglycemia and Hyperglycemia/Diabetic Ketoacidosis.

**Hypoglycemia:** Hypoglycemia is common in people with T1D. Clinically significant hypoglycemia (Level 2), defined as a blood glucose concentration of <3.0 mmol/L (<54 mg/dL) for at least 15 consecutive minutes in the CGM, typically leading to neuroglycopenic symptoms, will be reported as an AE if other causes, such as meal omission, unexpected increases in physical activity, or exercise, miscalculations of boluses by the participant or any other contributing factors, have been excluded. A diary for hypoglycemia events will be provided to participants for recording BG levels measured before treatment administration if taken, associated symptoms, treatment administered, and information about contributing factors, if applicable, as described previously.

Only severe hypoglycemia (or hypoglycemia level 3), defined as "a hypoglycemia event requiring medical assistance of another person due to altered consciousness and requiring another person to actively administer carbohydrate, glucagon, or other resuscitative actions" is reportable as an SAE. This means that the participant was impaired cognitively to the point that he/she was unable to treat himself/herself, was unable to verbalize his/ her needs, was incoherent, disoriented, and/or combative, or experienced seizure or coma. These episodes may be associated with sufficient neuroglycopenia to induce seizure or coma. If plasma glucose measurements are unavailable during such an event, neurological recovery attributable to restoring plasma glucose to normal is considered sufficient evidence that a low plasma glucose concentration induced the event.

**Hyperglycemic events/Diabetic Ketoacidosis (DKA):** Hyperglycemic event is only reportable as an adverse event when one of the following four criteria is met:

- 1) The event involved DKA, as defined by the Diabetes Control and Complication Trial (DCCT) and described here:

Hyperglycemic events are classified as DKA if the following are present (meeting all 4 criteria):

- a) Symptoms such as polyuria, polydipsia, nausea, or vomiting
  - b) Serum ketones >1.5 mmol/L or large/moderate urine ketones
  - c) Either arterial pH <7.30 or venous pH <7.24 or serum bicarbonate <15
  - d) Treatment provided in a healthcare facility.
- 2) Evaluation of treatment was obtained at a healthcare provider facility for an acute event involving hyperglycemia or ketosis.
  - 3) Blood ketone level  $\geq 1.5$  mmol/L and communication occurred with a health care provider during the event.
  - 4) Blood ketone level  $\geq 2.5$  mmol/L (even) without communication with a health care provider.

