##### **10.1.2.1 Foreseeable adverse events**

Hypoglycemia or hyperglycemia events not meeting the above criteria are not required to be reported as an adverse event.

Participant's own devices (e.g. insulin pump, CGM, BG meters) related issues and skin issues arising from using these devices (such as skin rash due to adhesive or infusion site issues) are not reportable unless the event meets the definition of an SAE.

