#### **Annex 4. General guidance on hypoglycemia management**

Participants will be encouraged to follow the guidance provided in **Annexes 2 and 3** to adjust the AID settings during the drug up-titration and observation period to minimize the risk for hypoglycemia.

- Each participant must have glucagon products with them as a part of the standard of diabetes care. The participants and caregivers (if any) will be trained on using glucagon products.
- Participants should be advised to follow treatment for hypoglycemia. if glucose <3.9 mmol/L (70 mg/dL), take 15 grams of carbs (or less as AID may have insulin suspension for anticipated hypoglycemia) and repeat after 15 minutes until glucose is >3.9 mmol/L (70 mg/dL).
- If a participant experiences clinically significant hypoglycemia events or severe hypoglycemia, it should be reported as AE (if criteria are met according to the study protocol) or SAE respectively . The AID settings should be adjusted to prevent another episode of hypoglycemia.

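### Section 10.1.2 limits hypoglycemia SAEs to Level 3 and the MESI text grades by severity; both contradict the outcome-based SAE definition in 10.1.1 and risk under-reporting of hospitalized or medically important Level 2 events

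*Protocol*

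**What the plan says.** Section 10.1.1 of the Protocol defines an SAE by outcome: death, threat to life, disability, congenital anomaly, or an event that "requires in-patient hospitalization or prolongation of existing hospitalization". Important medical events that may need intervention to prevent one of these are added. The Assessment of Severity text keeps intensity apart from seriousness: "Severe is a category utilized for rating the intensity of an event, and both AEs and SAEs can be assessed as severe". It goes on to say that an event is serious because it meets a listed outcome, not because it is rated severe.

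Section 10.1.2 then gives rules for glycemic events. Level 2 hypoglycemia (below 3.0 mmol/L for at least 15 consecutive minutes) "will be reported as an AE if other causes, such as meal omission, unexpected increases in physical activity, or exercise" and similar contributing factors have been excluded. For SAEs, the rule starts "Only severe hypoglycemia (or hypoglycemia level 3), defined as" an event with altered consciousness that needs active help from another person, and closes with "is reportable as an SAE. This means that the participant was impaired cognitively".

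Three further texts bear on this:
- Section 10.1.2.1: "Hypoglycemia or hyperglycemia events not meeting the above criteria are not required to be reported as an adverse event".
- The MESI text: "Overdose and missed insulin bolus resulting in severe hypoglycemia or hyperglycemia are considered AE or SAE, depending on severity".
- Annex 4, on clinically significant and severe events: "it should be reported as AE (if criteria are met according to the study protocol) or SAE respectively".

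**The concern.** The same hypoglycemic event can be judged by outcome (10.1.1), by level (10.1.2, echoed in Annex 4) or, after an overdose or missed bolus, by severity (MESI text). These tests do not give the same answer. A site looking up hypoglycemia will find the specific rule in 10.1.2, and its opening word is exclusive.

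Two things are at stake. One is prompt reporting: section 10.1.2.2 sends SAEs to the sponsor within 24 hours, and an event labeled as an AE, or not reported, does not take that route. The other is the safety analysis: section 11.4.5 compares any AE/SAE between arms, and that comparison is only as sound as the classification behind it. The trial is open-label and the protocol lists a data safety monitoring committee as not applicable, so consistent SAE classification matters more than usual.

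**Working it through.** No figure in the protocol is involved. The check is to put the same event through each rule and see whether the answers agree.

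**Case 1. Level 2 event, participant conscious and able to self-treat, admitted as an in-patient, no contributing factor found.**
- Section 10.1.1: SAE, because of the admission.
- Section 10.1.2: AE. The event is not Level 3, and only Level 3 qualifies as an SAE.
- Annex 4: AE, since clinically significant events are paired with AE and severe events with SAE.
- Result: conflict.

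**Case 2. As case 1, but the participant had skipped a meal.**
- Section 10.1.1: SAE. The definition does not depend on cause.
- Section 10.1.2: not an AE, because a contributing factor has not been excluded.
- Section 10.1.2.1: events outside the criteria need not be reported as an AE.
- Result: conflict, and wider than in case 1. An event that meets the SAE definition is not reportable under the specific rule.

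**Case 3. Level 3 event after an insulin overdose, rated less than severe in intensity.**
- Section 10.1.2: SAE, since Level 3 hypoglycemia is reportable as an SAE.
- MESI text: AE or SAE according to severity, so AE is permitted.
- Assessment of Severity: intensity does not decide seriousness.
- Result: conflict, if severe hypoglycemia in the MESI text means Level 3, as it does in section 10.1.2 and Annex 10.

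**Case 4. Acute hyperglycemia treated at a healthcare facility.**
- Section 10.1.2, second hyperglycemia criterion: reportable as an AE. No sentence restricts when it may be an SAE.
- Section 10.1.1: SAE if an outcome criterion is met.
- Result: no conflict.

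The surrounding text suggests an oversight rather than a deliberate narrowing. In 10.1.2.1, the sentence on the participant's own devices and skin issues keeps an exception for events that meet the SAE definition; the glycemic sentence next to it has none. Elsewhere in 10.1.2, hypersensitivity reactions become SAEs when any seriousness criterion is met, arrhythmias are referred to 10.1.1, and pancreatitis cases that do not meet all the stated criteria are left to the investigator's judgment of seriousness.

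**The case against.** The strongest reply is that nothing is necessarily lost. Section 10.1.2 opens by requiring that all AEs and all SAEs be collected and documented, section 10.1.2.2 requires every SAE to reach the sponsor within 24 hours, and the 10.1.1 definition is general and names hospitalization. An investigator who starts from 10.1.1 would report case 1 correctly. This stands, and it limits the point to a contradiction that could cause under-reporting. It does not remove the point, because those general sentences do not say which hypoglycemic events count as SAEs, while the specific rule does.

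The secondary texts are also softer than 10.1.2. Annex 4 does not say that only severe events are SAEs, and it defers to the protocol's criteria for AEs. The MESI text covers only overdose and missed bolus, and it describes a MESI as either an SAE or a non-serious AE, so its reference to severity may be loose drafting for seriousness. That is fair, and it is a reason to correct the words.

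A reader might infer several stronger things that the documents do not support:
- **Life-threatening events are lost.** The Level 3 description covers inability to self-treat, incoherence, disorientation, seizure and coma, and Annex 10 sets no glucose threshold for it. Few life-threatening events can lie below it.
- **Hospitalized hyperglycemia is lost.** Case 4 shows that it is not.
- **Hypoglycemia is the main foreseeable harm.** Section 3.7 names gastrointestinal disorders as the most recognized reactions and severe hypoglycemia as a rare risk. It accepts that tirzepatide may raise the risk of low glucose, but expects a frequency no higher than in daily life.
- **SUSARs would be missed.** A SUSAR must be unexpected, and the protocol treats hypoglycemia as a known risk.
- **The hypoglycemia signal disappears.** Section 11.4.5 compares clinically significant hypoglycemia separately, and time below 3.0 mmol/L is a secondary endpoint. What is at risk is reporting and the SAE label.
- **The effect is large because the arms are small.** With 21 per arm, one event is 1/21 = 4.8 percentage points, but that is true of any single event in this trial and says nothing about how often this one would occur.

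**Conclusion.** The protocol contradicts itself as written. The exclusive rule in 10.1.2 and the unqualified exemption in 10.1.2.1 cannot both stand beside the outcome-based definition in 10.1.1 for a Level 2 hypoglycemic event that leads to an in-patient stay or is an important medical event. The MESI reference to severity conflicts with the Assessment of Severity text and, for Level 3 events, with 10.1.2.

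The consequence is a risk of under-reporting and of inconsistent SAE classification in the 11.4.5 comparison. It rests on the assumption that a site applies the specific hypoglycemia rule in preference to the general definition, which is plausible but not certain. The size cannot be given, because the protocol states no rate for hospitalized or medically important Level 2 events. The point concerns reporting and classification only, not how hypoglycemia is managed. It should be corrected, because it bears on safety reporting and the correction is cheap.

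**What to change.** Reconcile the passages with four wording changes:
1. **Section 10.1.2.** State that Level 3 hypoglycemia is always an SAE, and that any other hypoglycemic event is an SAE if it meets a seriousness criterion in 10.1.1, whatever its level or cause.
2. **Section 10.1.2.1.** Extend to glycemic events the exception for SAEs that already applies to device and skin issues. For hyperglycemia this is only for consistency.
3. **MESI text.** Replace the reference to severity with a reference to the seriousness criteria in 10.1.1, keeping Level 3 hypoglycemia as an SAE.
4. **Annex 4.** Align it with the revised 10.1.2, so that a clinically significant event meeting a seriousness criterion is reported as an SAE.

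The cost is a protocol amendment and possibly a few more SAE reports. No extra data, visits or participants are needed.

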#### Adjudicated hepatic or pancreatic AEs (Pancreatitis)

The participants with a history of pancreatitis for any cause and risk factor for pancreatitis (e.g., alcoholism, triglycerides  $\geq 5.7$  mmol/L [ $\geq 500$  mg/dL]) will be excluded from this trial. However, acute pancreatitis is defined as an AE of interest in all trials with tirzepatide, including this trial. Acute pancreatitis is an acute inflammatory process of the pancreas that may also involve peripancreatic tissues and/or remote organ systems(104). The diagnosis of acute pancreatitis requires two of the following three features:

- 1) abdominal pain, characteristic of acute pancreatitis (generally located in the epigastrium and radiates to the back in approximately half the cases; the pain is often associated with nausea and vomiting).
- 2) serum amylase (total and/or pancreatic) and/or lipase  $\geq 3X$  ULN.
- 3) characteristic findings of acute pancreatitis on computed tomography (CT) scan or magnetic resonance imaging (MRI).

If acute pancreatitis is suspected, appropriate laboratory tests (including levels of pancreatic amylase [p-amylase] and lipase) should be obtained via the central laboratory (and locally, if needed). Imaging studies, such as abdominal CT scans with or without contrast, MRI, or gallbladder ultrasound, should be performed. If laboratory values and/or abdominal imaging support the diagnosis of acute pancreatitis, the patient must discontinue therapy with the study drug. The patient's concomitant medications should be reviewed to assess any other potential causal.

Each case of an AE of pancreatitis will be reported. If typical signs and/or symptoms of pancreatitis are present and confirmed by laboratory values (lipase or amylase [total and/or pancreatic]) and imaging studies, the event must be reported as an SAE. For a potential case that does not meet all these criteria, it is up to the investigator to determine the seriousness of the case (AE or SAE) and the relatedness of the event to the study drug.

#### Adjudicated hepatic or pancreatic AEs (Hepato-biliary disorders)

Hepato-biliary events will be considered AEs. All events of treatment, emergent biliary colic, cholecystitis, or other suspected events related to gallbladder disease will be evaluated, and additional diagnostic tests will be performed as needed. If a study participant experiences elevated ALT  $\geq 3X$  ULN, ALP  $\geq 2X$  ULN, or elevated TBL  $\geq 2X$ ULN, liver testing (**See Annex 9**) will be repeated within three to five days, including ALT, AST, ALP, TBL, direct bilirubin, and GGT to confirm the abnormality and to determine if it is increasing or decreasing. If the abnormality persists or worsens, clinical and laboratory monitoring will be initiated by the investigator and in consultation with the study medical monitor. ALT, AST, TBL, and ALP monitoring should continue until levels normalize or return to approximate baseline levels.

Additional safety data will be collected via the eCRF, and the IMP should be stopped if one or more of the following conditions occur:

- Elevation of serum ALT or AST  $>8$  times ULN
- Elevation ALT or AST  $>5$  times ULN for more than 2 weeks
- Elevation ALT or AST  $>3$  times ULN and TBL  $>2$  times ULN or INR  $>1.5$
- Elevation ALT or AST  $>3$  times ULN with the appearance of fatigue, nausea, vomiting, right upper-quadrant pain or tenderness, fever, rash, and/or eosinophilia ( $>5\%$ )
- Elevation ALP  $>3$  times ULN
- Elevation ALP  $>2.5$  times ULN and TBL  $>2$  times ULN
- Elevation ALP  $>2.5$  times ULN with the appearance of fatigue, nausea, vomiting, right quadrant pain or tenderness, fever, rash, and/or eosinophilia ( $>5\%$ )
- Elevated serum TBL to  $\geq 2X$  ULN (except for cases of known Gilbert's syndrome).

